### Measures

At recruitment, parents will be asked to complete an informed consent form confirming their participation in the study. The following measures will be administered at baseline, the end of the intervention and 6 months post intervention.

## Primary outcome

### Children’s knowledge about healthy eating, active play and the sustainability consequences of their food and toy selections

Children will be tested using a semi-structured interview based on the interview protocol used by [26] with 3–5 year olds to assess young children's healthy eating and active play knowledge. This will also include items investigating children’s understanding of sustainability concepts, such as waste and concepts of reduce, reuse, recycle and refuse (7Rs) [27]. A Research Fellow will interview children in a quiet area of their classroom, in full view of the teacher; teachers will be briefed to refrain from discussing which group they are in when the Research Fellow visits to ensure the Research Fellow is blind to randomisation.

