## Procedure

### The Teacher Intervention

Teachers participating in the intervention group will be provided with a copy of the pedagogical communication strategy and asked to develop a curriculum intervention that integrates content knowledge about healthy eating, active play and sustainability consciousness. They will then attend a professional learning session to orientate them to the project. This session will be hosted by the Chief Investigators. Each teacher’s curriculum intervention will be workshopped to ensure they have included the following components: 1) implementing the interventions over 1–2 days across a period of 3–4 weeks to build a solid portfolio of experiences and strong base for children’s discussions; 2) implementing the interventions in the morning when the children are most cognitively alert; 3) combining both whole group and small group experiences and discussions; 4) using ‘real world’ props/resources, such as cereal boxes, McDonald’s Happy Meal™ boxes and toys and merchandise; and 5) maintaining assessment records of children’s learning using Learning Stories [25], observation and documentation. Teachers will be provided with an ‘*Intervention Implementation Checklist’* and asked to record all components/elements associated with their curriculum interventions including: date, time, and duration of the intervention; the number of times the intervention or iterations of the intervention were implemented; Early Years Learning Framework Learning Outcomes aligned with the intervention; complete description of the intervention (including any resources/props used) and examples of any approaches to assessing children’s learning used in relation to the intervention. A booster session will be conducted 6 weeks after teachers implement their curriculum interventions whereby children will be exposed to an abridged version of the intervention.

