### Analyses

Baseline quantitative data (collected from parents) will be secured prior to treatment allocation, missing values will be scrutinized to check for non-random distribution and primary analyses will be executed twice: once using observed data, and once using multiple imputations under multivariate normal assumptions using methods given by [34], so that all participants will be analysed in their allocated condition. Analyses of variance (with corrections for potential clustering effects of individuals within childcare centres, [32]) will test the between group differences in the primary outcome measure (children’s knowledge about healthy eating, active play and the sustainability consequences of their food and toy selections; interview data will be quantified, after each child’s interview has been transcribed, for the analyses) and the secondary outcome measures (child eating and activity habits) at each assessment time point and across time points for the children. The teachers’ qualitative interviews 6 months post intervention will be analysed using elements of phenomenology and thematic content analysis [35-37]. A process evaluation will be undertaken to identify the key elements of the curriculum interventions that result in significant and positive shifts in children’s knowledge about healthy eating, active play and the sustainability consequences of their food and toy selections.

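### Asking teachers not to mention their group is the only stated safeguard for the primary-outcome interviewer's blinding, and it is not enough to ensure it; the stated masking also does not reach transcript scoring

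*Protocol article*

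**What the plan says.** Under Primary outcome, the protocol article describes the instrument as follows: "Children will be tested using a semi-structured interview". On the setting it says: "A Research Fellow will interview children in a quiet area of their classroom, in full view of the teacher". On masking it says "teachers will be briefed to refrain from discussing which group they are in when the Research Fellow visits", and gives the purpose as "to ensure the Research Fellow is blind to randomisation". No other measure to protect the interviewer's blinding is described.

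Under The Teacher Intervention, each intervention class receives a teacher-designed curriculum over 3–4 weeks. Required components include "using ‘real world’ props/resources, such as cereal boxes" and "maintaining assessment records of children’s learning using Learning Stories". Overall study design places the first follow-up directly after the intervention and the second 6 months later.

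Under Analyses, the primary outcome becomes a number only at a later step: "interview data will be quantified, after each child’s interview has been transcribed".

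**The concern.** The article claims that one instruction to teachers secures the interviewer's blinding. That instruction closes one channel, the teacher's speech. It leaves open what the interviewer can see in the room and what the children say. The children are questioned about the very subjects the intervention teaches.

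This matters because the primary outcome involves judgement at two steps: following up answers in a semi-structured interview, and converting a transcript into a score. If either step is done with knowledge of the arm, expectation can move scores towards the intervention. Baseline interviews precede delivery, so they cannot carry this effect; it would enter only at follow-up. Comparing groups across time points would therefore not remove it, and a positive knowledge effect could not be separated from assessor expectation.

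**Working it through.** The protocol gives no figure on masking to reproduce, so the check sets its sections side by side.

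**1. What the safeguard covers.** The briefing in Primary outcome is addressed to teachers and concerns what they say during visits. It does not address materials in the room or the children's remarks.

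**2. What could reveal the arm.** The Teacher Intervention requires props and documentation of learning in intervention classes. Primary outcome puts the interview in the classroom. Nothing says that materials are put away before a visit. A child asked about healthy eating, active play or waste may also mention the activities just completed.

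**3. When it applies.**
- Baseline: nothing has been delivered, so there is no such cue.
- End of intervention: the interview follows directly, so the cue is most likely here.
- Six months later: materials may be gone, and Participants says the children start primary school the following year, so the room may be different. The cue is weaker.

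**4. How many children per cue.** Recruitment strategy gives about 10 participants per preschool and 15 preschools per arm (18 after the attrition allowance). Allocation is by class, so recognising one class reveals the arm of about 10 children.

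**5. Where the masking statement stops.** It names the Research Fellow only. Analyses describes transcription and quantification without saying who scores or whether they see the arm.

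**6. A related point.** Qualitative interviews has the Research Fellow telephone six intervention-group teachers at 6 months, the time point of the last child interviews. The order of the two tasks is not given. If one person does both and the calls come first, that person learns those classes' allocation.

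**7. Why even a small bias would matter (illustration only).** Suppose there is no true effect and scores in the intervention arm are shifted by b SD. The inputs are 150 children per arm and 10 per preschool (protocol), with b and the intraclass correlation (ICC) assumed.

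- Design effect: DE = 1 + (10 − 1) × ICC, which is 1 at ICC 0 and 1.45 at ICC 0.05.
- SE = √(2 × DE / 150), which is 0.115 at ICC 0 and 0.139 at ICC 0.05.
- Rejection rate of a two-sided 5% test = 1 − Φ(1.96 − b/SE) + Φ(−1.96 − b/SE).

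| Assumed b (SD) | ICC 0 | ICC 0.05 |
|---|---|---|
| 0 | 5% | 5% |
| 0.1 | 14% | 11% |
| 0.2 | 41% | 30% |
| 0.3 | 74% | 58% |

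The table shows how sensitive the test is to a bias of a given size. It does not show that any such bias exists.

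**The case against.** The strongest reply is that much of the danger is inferred. Four stronger readings are tempting, and the documents do not support them.

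- *Props and records are kept or displayed in the interview room.* The Teacher Intervention says they are used and maintained, not where they are stored or whether they remain afterwards. The named props are everyday items. The Background says the national early-years framework already covers healthy eating and some environmental education, so control rooms may hold similar things.
- *Scoring is unmasked.* Analyses is silent. A condensed article may leave scorer masking to a fuller document, so silence is not evidence of its absence.
- *The investigators who train the teachers will code the transcripts.* Of the professional learning session the article says "This session will be hosted by the Chief Investigators", but no section assigns them coding.
- *The bias is 0.05–0.30 SD.* Such a range follows from assuming that 50–100% of intervention preschools are recognisable and that recognition shifts scores by 0.1–0.3 SD (0.5 × 0.1 to 1.0 × 0.3). Neither input is in the documents.

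It is also fair to say that the interview is based on an existing protocol for 3–5 year olds, whose probes may be tightly specified; that cannot be checked here.

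These replies limit the point but do not remove it. The article does more than leave masking unmentioned: it asserts that a named measure ensures blinding. That measure does not cover visible materials or children's remarks, whatever a fuller document may add.

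**Conclusion.** The point holds in limited form. The stated safeguard is insufficient for the property claimed: teachers' silence can support the interviewer's blinding but cannot ensure it when the interview is in the classroom straight after the intervention. Unmasking is possible, mainly at the end-of-intervention interview, and would affect about 10 children per recognised class. A reader might infer that blinding is bound to fail; the documents do not show that.

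On scoring, the conclusion is narrower still: the stated masking does not extend to that step, and the article does not say whether scorers are masked.

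The size of any bias cannot be derived from the documents. The rejection rates above rest wholly on an assumed bias applied across the intervention arm and an assumed ICC. The change is still worth making, because the primary outcome depends on judgement and the protection is cheap.

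**What to change.** **In Primary outcome:**
1. Ask teachers in both arms to clear or cover food, toy and sustainability materials and displays before every visit.
2. Hold the interview away from displays while staying within the teacher's sight.
3. Use fixed questions and a list of permitted probes.
4. Replace the claim that the briefing ensures blinding with a statement that it is intended to support it.

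**In Analyses:**

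5. Score transcripts with preschool, arm and time point removed, in random order, against a key fixed before follow-up begins.

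If the same Research Fellow makes the 6-month teacher calls, place them after the last child interview.

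**Cost.** A few minutes of tidying per visit, with no extra visit or interviewer. Transcript handling is real work: 300 children at three time points is 900 transcripts, and up to 360 × 3 = 1,080 if every recruited child is interviewed each time. Protection would remain incomplete, because some answers may still hint at the arm, and a scorer who interviewed the child or helped shape that class's curriculum may recognise the content.

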## Secondary outcomes

### Children’s food preferences, digital media viewing and physical activity habits

The Eating and Physical Activity Questionnaire (EPAQ) [28] that has been developed by Australian researchers and has been assessed against a 24-hour dietary recall in 90 parents of pre-schoolers and found to be valid and reliable [28]. This method of food recall has low participant burden (takes about 5–10 minutes to complete) and hence is both time and cost-efficient.

### Qualitative interviews

We will invite 6 teachers from the intervention group to take part in an interview to obtain qualitative data in relation to barriers associated with educator use of the pedagogical communication strategy. These interviews (conducted by the Research Fellow) will take place 6 months post intervention, and will inform us about the strengths of the curriculum interventions. Fifteen parents of children in the intervention group will also be invited to be interviewed at this point to examine their perspective on their children’s learning about healthy eating, active play and the sustainability consequences of their food and toy selections. All interviews will take place over the phone at a time that suits the teacher and parent.

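### As written, the plan does not protect the Research Fellow's blind for the 6-month primary-outcome interviews with the children

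*Protocol article*

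**What the plan says.** The Protocol article, Primary outcome, names the person who collects the primary outcome: "A Research Fellow will interview children in a quiet area of their classroom, in full view of the teacher". It then gives the one safeguard that it states for that person's blind: "teachers will be briefed to refrain from discussing which group they are in when the Research Fellow visits to ensure the Research Fellow is blind".

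The Measures section sets the schedule: "The following measures will be administered at baseline, the end of the intervention and 6 months post intervention". The child interview is one of these measures, so its final round falls at 6 months.

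The Qualitative interviews section then plans a second set of interviews: "We will invite 6 teachers from the intervention group to take part in an interview". The subject is barriers to using the strategy. On who does them and when, it says: "These interviews (conducted by the Research Fellow) will take place 6 months post intervention". A separate sentence adds: "Fifteen parents of children in the intervention group will also be invited to be interviewed at this point". That sentence does not name the interviewer. All of these interviews are by phone, at times convenient to the interviewee.

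In Analyses, the child data are scored from transcripts: "interview data will be quantified, after each child’s interview has been transcribed". The article does not say who does the scoring.

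**The concern.** The two roles do not fit together unless their order is controlled. One requires that the Research Fellow not know which preschools received the intervention. The other has the Research Fellow talk to teachers who were chosen because they delivered it. The invitation alone discloses the arm. The briefing under Primary outcome cannot help, because in these calls the teacher's use of the strategy is the topic.

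The exposed data matter. Hypotheses names 6 months post intervention as one of the two time points at which the arms are compared, and knowledge is the primary outcome. A semi-structured interview with 4 to 5 year-olds leaves room for prompting and follow-up to vary with what the interviewer expects. An interviewer who has just discussed the strengths of a teacher's curriculum is more likely to err in favour of the intervention than against it. Scoring from transcripts does not remove this, since prompting shapes the answers before they are transcribed.

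**Working it through.** The plan states no figure on this point, so there is nothing to reproduce. The check compares the sections and then counts the preschools that could be exposed.

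**Do the statements conflict?**

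| Feature | Child interviews | Teacher interviews |
|---|---|---|
| Interviewer | A Research Fellow, required to be blind | The Research Fellow |
| Respondents | Children in both arms | Intervention-group teachers only |
| Time point | Baseline, end of intervention, 6 months | 6 months |
| Order at 6 months | Not stated | Not stated; timed to suit the interviewee |

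The only overlap is at 6 months. The baseline and end-of-intervention child interviews are conducted before any qualitative interview.

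**How many preschools could be exposed?**

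Inputs:
- Teachers interviewed: 6 (Qualitative interviews).
- Intervention preschools: 15 (retained target) or 18 (recruited), in the same number of matched pairs (Recruitment strategy).
- Children per preschool: about 10 (Recruitment strategy).
- Assumption: one interviewed teacher per preschool. The article does not state this.

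Share of intervention preschools whose arm is revealed, at most:
- 6 / 15 = 40%
- 6 / 18 = 33%

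In children, at most 6 × 10 = 60, which is 60 / 150 = 40% or 60 / 180 = 33% of the intervention arm.

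These are upper limits for the teacher interviews. A preschool counts only if its teacher is contacted before its own 6-month child interviews are finished.

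**What would enlarge the count?** Two further conditions, neither of them in the text:
- If the Research Fellow knows which preschools are paired, each disclosed preschool also discloses its control partner: 12 / 30 = 40% or 12 / 36 = 33% of all preschools.
- If the Research Fellow also interviews the parents, there are up to 6 + 15 = 21 disclosing contacts against 15 to 18 intervention preschools. In the extreme case every intervention preschool is disclosed.

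The size of any resulting bias in the knowledge score cannot be computed from the article.

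**The case against.** The strongest reply is that nothing on the page says the teacher interviews come first. If the child interviews at each preschool were finished before its teacher was approached, they would have been conducted blind. A reader might infer that the blind is bound to be broken, and the article does not support that. It supports only the weaker statement that nothing in the plan prevents it. The reply does not remove the problem, because the order is left open and the calls are fitted to the interviewees' convenience. Child interviews in 30 to 36 preschools are also likely to be spread over some time (an inference), so overlap is a practical possibility.

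A second reply is that the two mentions of a Research Fellow could mean two people. That is possible. But the article speaks first of a Research Fellow and then of the Research Fellow, mentions no second one, and so reads most naturally as one person.

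A third reply concerns reach. A reader might infer that the Research Fellow also interviews the parents, or that matching discloses the control preschools too, so that a third or even all of the preschools are unblinded. The article names the Research Fellow only for the teacher interviews. It says that pairs exist, but not that the Research Fellow knows them. This reply stands, and the larger counts are conditional only.

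Finally, the absence of a named, masked scorer for the transcripts is a detail that a condensed article may leave to the full protocol. It is not part of the point.

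**Conclusion.** The point holds in a limited form. The article requires a blind interviewer for the primary outcome. It then gives that role a task at the 6-month time point that discloses allocation, with no stated order and no separate interviewer. The stated briefing of teachers cannot cover that task.

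The exposure is up to 6 of 15 to 6 of 18 intervention preschools (40% to 33%). This rests on three assumptions: one person holds both roles, there is one interviewed teacher per preschool, and contact with the teacher comes before that preschool's 6-month child interviews are complete.

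It would be wrong to conclude that the primary outcome as a whole is unblinded, since two of its three assessments are conducted before any of these calls. The risk is of a bias of unknown size, probably in favour of the intervention, at one of the two hypothesis time points. It is worth correcting because the correction is cheap.

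**What to change.** Add to Qualitative interviews: the Research Fellow makes no contact for teacher or parent qualitative interviews, including invitations, until the last 6-month child interview in every preschool is complete. Requiring this across all preschools, and not only the one concerned, also covers the case in which the pairings are known. Naming the parents covers the case in which the same person interviews them.

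The cost is one sentence and a short delay to at most 6 + 15 = 21 phone interviews. The article does not say how long the 6-month child interviews will take, so the delay cannot be stated more precisely. No extra staff are needed.

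Giving the qualitative interviews to the Chief Investigators, who already know the allocation from hosting the professional learning session, is less attractive. The strategy was developed by the study team, and teachers may be less frank about barriers when its developers are asking.

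Optional: score the child transcripts with arm masked. This would also keep the scoring blind if the Research Fellow does it after the qualitative interviews.

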### Anthropometry

Height and weight will be measured with a stadiometer and standardised digital scales, respectively, at all assessments for children. Children will be weighed each time wearing light clothing and no shoes. Height and weight measures will then be converted to a Body Mass Index (BMI, kg/m2) for each participant. Body Mass Index will be standardised for age and gender using BMI-for-age z-scores and change will be assessed using BMI z-score slope [29] following WHO recommendations for children this age [30].

### Power, sample size and retention

The primary outcomes for this intervention are children’s knowledge about healthy eating, active play and the sustainability consequences of their food and toy selections. However, we decided to power our sample for the secondary outcome of child eating because we wanted to evaluate the extended effect of delivering the curriculum interventions to preschool children and we could base our sample size calculations on Australian data that provide relevant parameter estimates from three studies in the Barwon-South Western region of Victoria (*n* = 950) with children aged 2–4 years of age [31]. Vegetable consumption will require the largest sample size to demonstrate change over time, compared to other dietary outcomes, such as sweetened drinks, packaged snacks (e.g., chips, muesli bars), confectionary/chocolate, cake/sweet biscuits, and fruit, based on sample size analyses. As there are no quantitative dietary recommendations for children less than 4 years old in Australia, we adopted a suggestion of a 25% increase in vegetable consumption as a minimum target [32]. Based on findings that 63% of pre-school children had ≤1 serve of vegetables per day, we assume that the intervention will have a 25% absolute effect, that is the proportion of children in the intervention group who only have ≤1 serve of vegetables per day will change from 63% to 43%. We calculated the sample size necessary to detect a clinically meaningful difference in vegetable consumption, significant at the 0.05 level, with a power of 0.8; this calculation resulted in a sample of 150 children in each group. Making a prudent allowance for attrition of 20% (based on our previous research with preschool children and their parents), the adjusted number per treatment condition is 180. A total of 360 4-year-old children will therefore be recruited. This sample size is also sufficient to detect medium effect sizes in both the primary and secondary measures with a power of .8 at α = 0.05 [33].

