### Recruitment strategy

The study will consist of at least 30 of the 68 available preschools (from Early Childhood Services Management (ECMS), Victoria) and aims to retain a total of at least 300, 4–5 year old children, who attend preschool together with their English speaking parents (because the program is only offered in English); the children will be in their final year of preschool. With a likely quota of 10 participants per preschool, 30 preschools (15 matched pairs) are required, 15 randomized to each arm of the study. Our formative work indicated a potential 11% attrition rate. Making a prudent allowance for attrition of up to 20%, 360 4–5 year old children and their parents will therefore be recruited and the adjusted number of preschools per study arm is likely to be 18 (i.e. a total of 36 kindergartens in 18 pairs).

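### The planning effect is worded as 25% absolute but printed as 63% to 43% (20 points), and neither printed version gives 150 per group without an unstated clustering allowance

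*Protocol article*

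**What the plan says.** The calculation is in the protocol article under *Power, sample size and retention*. It is made for a secondary outcome, child eating, and within that for vegetable consumption, which the section says needs the largest sample of the dietary outcomes.

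- Origin of the 25%: "we adopted a suggestion of a 25% increase in vegetable consumption as a minimum target".
- Starting rate: "Based on findings that 63% of pre-school children had ≤1 serve of vegetables per day".
- Effect in words: "we assume that the intervention will have a 25% absolute effect, that is the proportion of children in the intervention group".
- Effect in figures, in the same sentence: "≤1 serve of vegetables per day will change from 63% to 43" per cent.
- Result, for power 0.8 at the 0.05 level: "this calculation resulted in a sample of 150 children in each group".

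The section gives no ICC, no design effect and no sidedness. *Recruitment strategy* supplies the cluster structure: "With a likely quota of 10 participants per preschool, 30 preschools (15 matched pairs) are required", with 15 preschools in each arm. *Analyses* provides for a correction for clustering within centres, but only for the analysis.

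**The concern.** One sentence gives the planning effect twice, and the two versions disagree. A drop from 63% to 43% is 20 points. A 25-point drop would end at 38%, and a 25% relative drop at 47.25%.

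The stated sample size should show which was meant, but it matches neither printed version. So a reader cannot tell what difference the 80% power refers to, or whether the 150 already allows for randomising whole preschools. The possible explanations point in opposite directions: under the printed rates there is room for clustering, and under a relative reading there is none.

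This is the only calculation in the article with its inputs shown. The 150 per group carries through to the 30 preschools, and to the 360 children and 36 preschools after the attrition allowance.

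**Working it through.** **Inputs from the article.** Starting rate 63%, taken here as the rate that the control group keeps; end rate 43% as printed, or 38% as worded; alpha 0.05; power 0.80; 150 per group; equal allocation; m = 10 children per preschool. **Assumed:** a two-sided test, and any ICC value, since the article gives neither.

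**Size of the effect.** 63 − 43 = 20 points, and 20/63 = 32% relative. 63 − 25 = 38. 63 × 0.75 = 47.25.

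**Sample size per group, no clustering.** Pooled two-proportion formula, with p̄ the mean of the two rates:

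n = [1.960·√(2p̄(1−p̄)) + 0.842·√(p₁(1−p₁)+p₂(1−p₂))]² / (p₁−p₂)²

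For 63% versus 43%: [1.960·√0.4982 + 0.842·√0.4782]² / 0.04 = (1.383 + 0.582)² / 0.04 = 96.6, so 97.

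| Rates | Reading | n pooled | n unpooled | Power at 150 |
|---|---|---|---|---|
| 63 vs 43 | figures as printed | 97 | 94 | 93.8% |
| 63 vs 38 | 25 points, as worded | 62 | 59 | 99.3% |
| 63 vs 47.25 | 25% relative, not printed | 156 | 153 | 78.6% |
| 63 vs 47 | the same, rounded | 151 | 148 | 79.9% |

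Other conventions do not rescue the printed rates. For 63% versus 43%, a continuity correction gives 107, 90% power gives 129 (139 with the correction), and a one-sided test at 80% power gives 76. The stated 150 is therefore not reproduced from either printed effect. It is reproduced closely by the relative reading with no design effect.

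**Design effect needed to reach 150.** DE = 1 + (m − 1)·ICC.

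- 63 vs 43: 150/97 = 1.55, so ICC = 0.55/9 ≈ 0.06.
- 63 vs 38: 150/62 = 2.42, so ICC = 1.42/9 ≈ 0.16.

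These ICCs are solved backwards from 150. They are not values that the article states.

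**Power at 150 per group with clustering.** Effective size = 150/(1 + 9·ICC), then

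power = Φ{[(p₁−p₂)√n_eff − 1.960·√(2p̄(1−p̄))] / √(p₁(1−p₁)+p₂(1−p₂))}

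| Assumed ICC | DE | 63 vs 43 | 63 vs 38 | 63 vs 47.25 |
|---|---|---|---|---|
| 0 | 1.00 | 94% | 99% | 79% |
| 0.02 | 1.18 | 90% | 98% | 72% |
| 0.06 | 1.54 | 80% | 94% | 60% |
| 0.10 | 1.90 | 72% | 89% | 51% |

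This is a simple unmatched comparison at one follow-up time.

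**The case against.** The best defence is that only the label is wrong. If the trial was planned on 63% to 43%, then 150 exceeds the unclustered 97 by a margin that suits a modest clustering allowance. The article plainly knows that it has clusters: it fixes 10 per preschool, plans matched pairs and corrects for clustering in the analysis. A journal article may leave the ICC to the full protocol, so its absence alone is not a fault. This stands, and the point does not rest on the missing ICC. It rests on two statements of the effect that cannot both be true, and on a sample size that follows from neither as printed.

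Three stronger conclusions are tempting, and the article does not support them.

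- *That 150 follows from no reading at all.* A 25% relative reduction gives 148 to 156 without any design effect.
- *That the trial is underpowered.* That needs the relative reading, which is inferred from the match with 150 and printed nowhere, together with assumed ICCs. Under 63% versus 43%, power stays at about 80% or more up to an ICC of about 0.06; under 63% versus 38%, up to about 0.16.
- *That the planners used an ICC of 0.06.* That value is only what makes 97 into 150.

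The power table also ignores the matched pairs and the baseline measurements, either of which could change the power at a given ICC.

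**Conclusion.** The contradiction is certain: the wording says 25 points and the figures say 20. Neither gives 150 per group at 80% power unless a design effect of about 1.55 or 2.4 was applied and left out. The relative reading explains the 150 most directly, which suggests that *absolute* and 43% may be slips, but does not prove it. If that reading is right, the figure contains no clustering allowance and the 80% claim does not hold for this design: power is about 72%, 60% and 51% at ICCs of 0.02, 0.06 and 0.10 for 63% versus 47.25%.

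These results assume a two-sided test, 10 children per preschool and an unmatched comparison at one time point; the ICCs are illustrative. The text should be corrected. Because the calculation concerns a secondary outcome and can be restated without touching the design, this is not a reason to hold up the trial.

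**What to change.** Reconcile the effect, the two rates and the sample size under *Power, sample size and retention*:

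1. Replace the 25% absolute wording with the effect actually used, and make both rates agree with it. If 63% to 43% was used, call it a 20 percentage-point absolute reduction.
2. State the sidedness, the sample size per group before clustering, and the ICC or design effect actually applied, or say that none was applied. The back-solved ICC of 0.06 must not be entered as the planning value unless the sponsor's records show that it was.
3. Restate the power at 150 per group over a range of ICCs. If a 25% relative reduction was used with no clustering allowance, say that the power is below 80%.

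The cost is a few reworded sentences and a small table, and possibly a less favourable stated power. Recruitment need not change.
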